#### Other outcome measures

The range of measures we have included reflect the fact that mental health in infancy is multi-faceted and the various aspects (relationship, psychiatric diagnoses, cognition and language) overlap with one another [45].

The Infant-Toddler Social-Emotional Assessment (ITSEA) is a well-validated parent/carer-completed questionnaire covering a wide range of social and emotional behaviours in infants and pre-school children [46]. It has been shown to be sensitive to change in previous intervention research with maltreated children with medium to large effect sizes [47] and has good longitudinal stability.

Because mental health in pre-school children is so linked to cognitive functioning, we have included a full-scale IQ measure (see Table 2), WPPSI [48], measured at age 2.5 years. WPPSI is a well-validated and commonly used measure for this age group and covers both performance and language aspects of cognition.

**Table 2 Tab2:** Study procedures

Study procedure	Visit 1	Visit 2	Randomisation automated system	Visit 3 (baseline) ***4–14 weeks post-care entry***	Visit 4 (follow-up) ***15 months post-care entry***	Visit 5 (final follow-up) ***2.5 years post-randomisation***	Interview or focus group
Provision of study information	✓	✓					
Consent		✓					
Randomisation			✓				
SDQ *To be completed for children aged 2 and over, according to age of child:* *• 2*–*4y, 4–17y*				✓	✓	✓	
PIR-GAS *To be completed for all children*				✓	✓	✓	
ITSEA *To be completed for children aged 12–35 months*				✓	✓		
DAI *To be completed if child 12 months and over*				*✓*	*✓*	*✓*	
DAWBA *To be completed for children aged 2 and over, according to age of child:* *• 2*–*4y, 4–17y*				✓	✓	✓	
Service use questionnaire *To be completed for all children*				✓	✓	✓	
TIMB *To be completed for all children*				✓	✓	✓	
Observational Checklist for RAD *To be completed if child 12 months and over*				✓	✓(if not collected V3)		
Cognitive assessment • *WPPSI III—30–47 months,* • *WPPSI III—48–87 months* • *WISC IV—children + 87 months*				✓ (optional)	✓ (optional)	✓	
PedsQL *To be completed for all children, according to age of child:* • *1–12 m, 13*–*24 m, 2–4y, 5–7y*				✓	✓	✓	
RPQ *To be completed if child 12 months and over*				✓	✓	✓	
Data linkage						✓	
Parent/carer qualitative interview/focus group							✓

Psychiatric diagnoses will be assessed using the Development and Wellbeing Assessment (DAWBA)—a validated semi-structured interview generating ICD and DSM diagnoses [49].

The Relationship Problems Questionnaire [50] and the Disturbances of Attachment Interview (DAI) [51] will be used to investigate Reactive Attachment Disorder (RAD) symptoms. The Observational checklist for RAD [52] will be used, alongside these measures, to establish diagnoses of RAD.

Because the commitment of carers to their child has been shown to be related to the quality of the relationship [53], we will use the This is My Baby (TIMB) questionnaire—a brief questionnaire investigating carers’ long-term view of their relationship with the child [54].

In order to adhere to the recommended methods for economic evaluation of public health interventions by the National Institute for Health and Clinical Excellence (NICE) [55], the PedsQL, a validated measure of child Quality of Life [56], will be included with the intent to map outcomes to EQ-5D utility so as to estimate quality-adjusted life years (QALYs). Recent work by Khan et al. [57] has mapped EQ-5D utility scores from the PedsQL generic core scales; hence, these algorithms will provide an empirical basis for estimating health utilities in this population.

Linkage with routine data will allow us to measure repeat episodes of maltreatment and validated physical and mental health diagnoses. Consent for this is sought at recruitment.

Our assessment of effectiveness and cost-effectiveness, based on our primary outcome (mental health), will be measured at 2.5 years after randomisation. We have chosen this time point because, by then, the great majority of children should be settled in a permanent placement (either in a rehabilitated birth family or in an adoptive family). While even the children who were youngest at entry to care will, by this time, be of an age where a valid psychiatric and cognitive assessment can be made using measures that could be repeated at older ages if funding were found to continue following the cohort after this study is complete.

### Participant timeline {13}

Study procedures are summarised in Table 2.

### Sample size {14}

Initially, the target sample size was 492 families to achieve 90% power with a loss to follow-up of 75% [25]. Although 80% power is usual, the Glasgow clinical trials unit routinely powers trials at 90%, especially for complex studies such as this where allowance is needed to be made for unexpected loss to follow-up and missing data. However, the feasibility trial showed that 2.5-year follow-up was > 70% so, when varying the contract with the funder, a revision was made such that our target is now 80% power. Our estimated sample size to achieve 80% power with a loss to follow-up of 30% is 396 families.

### Recruitment {15}

This study uses the novel recruitment and retention strategy of employing experienced social workers, who receive additional specific training in Good Clinical Practice, to screen for eligibility and conduct our study information and consent meetings with potential participants. This is important for several reasons: (1) Social workers are already well trained in engaging with families undergoing crises, in evaluating whether a potential participant is competent to give consent and, if not, whether there are supports that can be put in place to ensure competence (e.g. the presence of an advocate, returning once the participant has had time to discuss the study with a trusted person). (2) Experienced social workers are confident in approaching “gatekeepers”, such as other social workers or their managers, to explain the study and facilitate the opportunity for potential participants to be informed. (3) Social workers have access to data systems that can give crucial information about the whereabouts and life circumstances of potential participants to ensure that it is ethical and safe to conduct an information meeting, or to approach a participant for follow-up.

In addition, in each site, efforts have been made to build good relationships with the most senior social worker in charge of child protection and to involve that person in the local steering group. This is important because these senior managers can mandate that every eligible family in their area should be informed about the study; they can trouble-shoot challenges regarding recruitment and retention with colleagues in other areas during steering group meetings; and they can authorise the research team having access to social work data systems.

## Assignment of interventions: allocation

### Sequence generation {16a}

Random allocation of families will be performed using a mixed minimisation/randomisation method, stratified within the study site. A randomisation schedule will be prepared for each site, in blocks of 10: in each block, 8 allocations will be decided by minimisation, and two at random (one to each group). For those to be minimised, the schedule will indicate which group to allocate to in the case of “no preference” according to the algorithm (4 to each group, at random).

Minimisation is designed to ensure balance of allocations with respect to study site, the age of the youngest child coming into care at the point of randomisation (< 2/≥2 years), the number of children coming into care at the point of randomisation (1/> 1), whether the birth family is fluent in English and the type of care (i.e. foster or kinship)

### Concealment mechanism {16b}

Randomisation is conducted via a Web portal, which requires a log in and password, and is managed by the Robertson Centre for Biostatistics, University of Glasgow. Access rights are allocated to relevant staff, as listed on the trial delegation log, in advance of the randomisation procedure.

### Implementation {16c}

Participants are enrolled on the randomisation system by recruitment coordinators. Recruitment coordinators, trial managers and nominated contacts per site and per arms of trial are automatically informed of the intervention allocation by email. Recruitment coordinators inform the social worker managing the families’ case of arm of trial, and the social worker will then work with the family to manage access to the arm of trial.

## Assignment of interventions: blinding

### Who will be blinded {17a}

The study is single blind. Participants will be aware to which arm of trial they have been allocated. Researchers and statisticians will not. For questionnaire and interview measures, we have incorporated a system whereby the research assistants have a script that they use as families are invited to assessments that aims to ensure they do not reveal intervention allocation (e.g. by stating the location at which parenting capacity assessments were conducted). Following assessment visits, research assistants state which intervention they think the family were attending so that, at the end of the study, we can assess the degree to which these blinding measures were successful. Parenting quality assessments (PIR-GAS) and Time to Permanent Placement are fully blinded since PIR-GAS is rated by individuals who have no access to group allocation and TTPP through examination of social work data, again by individuals with no access to group allocation.

### Procedure for unblinding if needed {17b}

Unblinding is permitted by the independent members of the Data Monitoring and Ethics Committee (DMEC) and, should they wish to become unblinded, these data will only be discussed during closed meetings of the DMEC.

## Data collection and management

### Plans for assessment and collection of outcomes {18a}

Standard operating procedures will be produced for the collection of each measure, and these will be included in training documentation and the study manual. All research nurses or psychologists will be trained in administering study measures and will practice administration of measures with each other prior to conducting research assessments.

All data will be collected using standardised paper case report forms (CRF) based on the individual instruments being used. These will be version controlled.

For the measures requiring rating, more extensive training will be offered until raters achieve sufficient reliability. Once trained to reliability, inter-rater reliability will be regularly checked according to a standard operating procedure in which 10–20% of tests will be randomly selected for independent rating by a second rater. Any difficult ratings, or ratings for which independent raters do not sufficiently agree, will be brought to an approximately 3-monthly conference with an expert rater. The proportion of ratings requiring conferencing will be recorded. Data collection forms are available on request.

### Plans to promote participant retention and complete follow-up {18b}

Because the study population are families with a wide range of social and psychological difficulties, it will be essential for the research team to have access to social work datasets for tracking purposes and to employ experienced social workers to re-engage with families at follow-up. All attempts will be made to gather data from consented families, including those who have failed to adhere to intervention protocols. Repeated attempts to contact participants will be made by phone and, later, in “drop-in” visits—each time leaving instructions regarding how to text or phone the team if the participant no longer wishes to participate in that assessment. Unless participants have stated that they do not give consent, routine data (e.g. for Time to Permanent Placement) will be gathered, even if participants do not respond to attempts to contact them.

### Data management {19}

All data handling procedures will be detailed in a study-specific data management plan.

All data collected will be stored securely, in accordance with the University of Glasgow Best Research Practice Guidelines, and managed in accordance with the Data Protection Act 1998 and the General Data Protection Regulation (from May 2018), in either locked filing cabinets or password-protected databases. Data will be accessible only by members of the UoG research team and their research partner KCL. All quantitative data collected as part of the study will be securely transferred to the Robertson Centre for Biostatistics CTU for data entry and checking in accordance with their SOPs. Qualitative interview data will be transcribed by an external transcriber and securely stored.

Data will be validated at regular intervals during the study. Data discrepancies will be flagged to the study site, and any data changes will be recorded to maintain a complete audit trail (reason for change, date change made, who made change).

### Confidentiality {27}

All data collected will be kept separate from any individual participant identifiers and secure. Participants will be assigned a unique ID number to link their data throughout the trial.

### Plans for collection, laboratory evaluation and storage of biological specimens for genetic or molecular analysis in this trial/future use {33}

No biological specimens will be collected.

## Statistical methods

### Statistical methods for primary and secondary outcomes {20a}

The primary analysis will use a generalised linear mixed effects regression model for the primary outcome measure to account for clustering of outcomes within families and adjusting for child age and other minimisation factors. The primary outcome measure is the Total Difficulties scale of the SDQ at 2.5 years after entering care. All models will be adjusted for age at the point of completion.

A single model over all three time points will be fitted. Interaction terms will be used to assess whether intervention effects vary between subgroups. The level of significance for the primary outcome is 0.05. A detailed Statistical Analysis Plan will be prepared and approved prior to database lock and unblinding of intervention groups.

We are analysing the trial on an intention-to-treat basis. Families who re-enter the study will not be re-randomised and, if appropriate, will receive assessment and treatment by the team to which they were previously randomised.

Blinded data analyses will be carried out during the trial, to determine the most appropriate method of allowing for clustering of outcomes within families. All modelling decisions taken during blinded analyses will be documented and approved prior to database lock. If modifications to the analysis are required following database lock, these will be documented and justified within the final statistical results.

### Interim analyses {21b}

No interim analyses are planned, other than blinded analyses to determine whether data need to be transformed prior to analysis, or if an alternative link or variance functions are required within the model. These modelling decisions will be documented and approved prior to database lock. While we do not consider it necessary to pre-specify stopping rules, as the feasibility trial has not suggested any harm, data monitoring is the responsibility of the Data Monitoring and Ethics Committee which can examine unblinded data and recommend stopping the trial if thought necessary at any point during the study.

### Methods for additional analyses (e.g. subgroup analyses) {20b}

The following subgroups will be considered:
Study siteDeprivation, as determined by (Scottish) Index of Multiple Deprivation quintilesAge of youngest eligible child coming into care at the point of randomisation (< 2/≥2 years)Age of individual children (< 2/≥2 years)Number of eligible children coming into care at the point of randomisation (one/more than one child)Birth family fluency in EnglishSexRandomisation system in place at the time of randomisation

The primary and secondary outcomes will be summarised overall and by randomised group, separately within each subgroup, and the primary and secondary analysis regression models will be extended to include intervention-by-subgroup interaction terms, to estimate intervention effects within subgroups, and to test for heterogeneity in intervention effects between subgroups.

### Methods in analysis to handle protocol non-adherence and any statistical methods to handle missing data {20c}

Analyses will be according to the intention to treat principle, in that they will be in relation to randomised allocation, regardless of compliance with the allocated intervention. As a pragmatic trial, it is unlikely that any protocol deviations will necessitate removal of any participants from analysis. However, protocol non-adherences will be logged with the clinical trial unit and will be assessed for their impact on the scientific integrity of the trial.

Missing outcome data will not be imputed in the main analyses, though the primary analysis is based on a linear mixed effects regression model which accounts for missing data, and sensitivity analyses will be carried out to (a) assess alternative assumptions regarding missing outcome data and (b) use multiple imputation methods, assuming data are missing at random from questionnaires.

### Plans to give access to the full protocol, participant-level data and statistical code {31c}

When the trial is completed, requests can be made for an anonymised version of the dataset.

## Oversight and monitoring

### Composition of the coordinating centre and trial steering committee {5d}

The study coordinating centre is the Glasgow Clinical Trials Unit (CTU Registration Number 16). Day-to-day trial coordination is conducted by the chief investigator and senior trial manager, with oversight of the entire study, and the English site is coordinated by a London principal investigator and London trial manager. The entire Glasgow and London research team (both trial managers, chief and principal investigator, Glasgow and London recruitment coordinators and Glasgow and London research nurses) will meet approximately monthly during the most intense periods of recruitment and retention and less frequently during less intense periods of the study. The process evaluation team (Glasgow based) will meet approximately every 6 weeks and there will be frequent (at least weekly) ad hoc meetings between trial managers and various members of the study team. The trial management group (comprising the co-investigators) will meet approximately quarterly, with two of the meetings each year timed to just precede the six-monthly data monitoring and ethics committee meetings which will precede the six-monthly trial steering committee meetings. Additional DMEC and TSC meetings can be convened on an ad hoc basis if there are specific urgent issues to discuss.

### Composition of the data monitoring committee, its role and reporting structure {21a}

A Data Monitoring and Ethics Committee will act as the oversight body for this trial with its primary roles being to safeguard the interests of trial participants, monitor the main outcome measures including safety and efficacy, and monitor the overall conduct of the trial.

The committee compromises 3 independent members, one of whom is the chair. Independent members are nominated to and approved by the funder. Members are chosen for their expertise in conducting relevant research. The independent members include a statistician and a psychiatrist. The committee facilitator is the trial manager. Other attendees include the chief investigator and trial statistician. The committee will meet at least annually and reports to the funder. The charter is available upon request.

### Adverse event reporting and harms {22}

To ensure that serious adverse events relevant to the trial are captured, the study team will review participants’ case notes on a six-monthly basis for the presence of serious adverse events. Deaths as recorded in routinely available health data in Scotland will also be examined. All SAEs arising during the trial will be recorded as soon as reasonably practicable after the site first becomes aware of the event.

Many participants and their birth parents taking part in the trial will have complex medical and mental health histories. Therefore, many adverse events and serious adverse events would be expected to occur within the participant group irrespective of their involvement within the study. These expected events do not necessarily require reporting to the Research Ethics Committee as serious adverse events but will be monitored by the trial team in relation to differential rates across trial arms, via the usual health and social care processes to ensure participant safety, and details recorded in a log. Their relatedness will be assessed by the chief investigator and, 6 monthly, by a small panel of experts (including a consultant paediatrician). The Data Monitoring and Ethics Committee (DMEC) will review these six-monthly.

Any SAE occurring to a research participant (or, in the case of deaths, also, their birth parent) where in the opinion of the chief investigator (CI), the panel of experts or the DMEC, the event was “Related”—that is, it resulted from the administration of any of the research or intervention procedures, and “Unexpected”—that is, the type of event is not an expected occurrence, will be reported by the Pharmacovigilance office to the Research Ethics Committee that approved the trial.

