### Eligibility criteria {10}

#### Inclusion

Families are eligible for the trial if they have a child aged 0 to 60 months who enters care in the recruiting sites for reasons associated with maltreatment, during the study recruitment period. Participants are included in the trial upon completion of written informed consent from the birth family and the child’s foster or kinship family.

In the event of a subsequent child being taken into care among participating families, consent will be sought from parent(s) and carers to include the new child. If consented, the new child will not be randomised, but will instead be allocated to the same arm of trial as their previous family members. This is partly to avoid contamination, but also because the aim of NIM is to help the parent(s) become more nurturing for both the current and any future children, and if a parent has already had NIM, it might be confusing for them to receive an intervention with a different and potentially contradictory ethos.

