#### Exclusion

Families will be excluded from the trial if the parent(s) is unavailable to take part in an intervention (for example, because of death, unknown whereabouts or long-term imprisonment).

If a family has been randomised previously but became ineligible without being exposed to either of the study interventions, then the family may be randomised again, should they become eligible at a later date.

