### Additional consent provisions for collection and use of participant data and biological specimens {26b}

We take consent to access routinely collected health and social work data about the child and parent. Any specific requests for routine data from central sources (e.g. NHS or legal system routine data) will require a separate application and be governed under information governance legislation by the relevant bodies. The data will be used to monitor safety throughout the trial, to examine the representativeness of the trial sample, to augment the planned health economics analysis and to monitor current placements of children in the study to enhance retention rates at follow-up.

Data contributing to our time to permanent placement secondary outcome measure are gathered, blind to arm of trial, from social work and legal system records. These data include dates and recommendations of the parenting capacity assessment received, dates and recommendations made at permanence hearings, placement details and legal orders after permanence decisions were made.

In addition, routine data will be used as part of the process evaluation, for example to examine how the social care and legal context is related to children’s journeys through placement and to their mental health. This is described in a separate process evaluation protocol paper [29].

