### Intervention description {11a}

The experimental intervention is NIM, which aims to improve the mental health of young, maltreated children. It has a US evidence-base, although not derived from an RCT [34]. NIM is an intensive, targeted, individualised, family-based intervention that aims to offer assessment and trial-of-treatment for the birth family and make timely recommendations for rehabilitation back to the birth home or adoption.

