The NIM intervention is as follows: a multidisciplinary infant mental health team comprising psychologists, a psychiatrist, other therapists and social workers assesses the mental health and relationship quality of children under 5 years of age upon reception into care. The assessment, which involves each actual and potential caregiver, is manualised and standardised and uses structured interviews, self-report measures and observations. A multidisciplinary meeting is then held to decide if it is appropriate to proceed to a tailored trial-of-treatment. Wherever possible, treatment is offered to each family, drawing on a small range of relationship-based therapeutic techniques all of which comply with the recommendations of a meta-analysis that examined ways of improving parental sensitivity [38]. Parents are also referred as required to other agencies for help with substance misuse, mental health issues or intra-familial violence. These assessments, and the degree of change achieved during the trial-of-treatment, inform recommendations to the legal system about the permanent future care of the child. The aim is to have “the best outcome possible for [the] particular child” ([name], personal communication, 2014), be this a recommendation of rehabilitation to birth family or adoption [34]. Where significant change has been achieved, children are rehabilitated back to the birth family. If not, the recommendation is adoption. Throughout the time that birth families are receiving the intensive intervention, the child remains in a nurturing placement with foster carers who are ideally willing to adopt the child if necessary, although the feasibility trial has shown that foster carers being dually registered as adopters is rare in the UK [39].

In this definitive trial, NIM will be delivered by the Glasgow Infant and Family Team (GIFT) and the London Infant Family Team (LIFT).

A logic model for NIM (Fig. 1) was developed in collaboration with the developers (Professors [name] and [name]) prior to the feasibility RCT and may be modified, as a result of process evaluation findings, prior to any roll-out of NIM should it be proven cost-effective.

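### As most naturally read, the rule on reporting Related and Unexpected SAEs to the REC covers birth parents only when they die, although parents consent and are directly assessed and offered treatment; at best the rule is ambiguous

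*Protocol article*

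**What the plan says.** Under Adverse event reporting and harms {22}, the protocol article sets the scope of REC reporting as "Any SAE occurring to a research participant (or, in the case of deaths, also, their birth parent". The event must also be judged Unexpected and Related, and Related means that "it resulted from the administration of any of the research or intervention procedures". The chief investigator, the expert panel or the DMEC makes that judgement.

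The same section explains why many events are expected: "Many participants and their birth parents taking part in the trial will have complex medical and mental health histories".

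Elsewhere the article describes what the trial asks of birth parents:

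- Inclusion: "Participants are included in the trial upon completion of written informed consent from the birth family", together with consent from the foster or kinship family.
- Exclusion: "Families will be excluded from the trial if the parent(s) is unavailable to take part in an intervention".
- Intervention description {11a}: NIM "aims to offer assessment and trial-of-treatment for the birth family and make timely recommendations for rehabilitation back to the birth home or adoption". On treatment: "Wherever possible, treatment is offered to each family".
- Additional consent provisions {26b}: "We take consent to access routinely collected health and social work data about the child and parent".

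**The concern.** The definition of Related reaches every research or intervention procedure, and many of those procedures are applied to the birth parent. The reporting rule, as most naturally read, follows the parent only as far as death. A serious non-fatal event in a consenting parent, such as a psychiatric admission, could be judged to result from trial procedures and to be of an unexpected type, and still have no stated route to the committee that approved those procedures.

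What is at stake is oversight of adults who take part. An event of that kind is what an REC would need in order to reconsider its approval or the information given to parents.

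**Working it through.** No arithmetic applies. The check sets the relevant sections side by side.

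**1. Who the rule covers.** In "Any SAE occurring to a research participant (or, in the case of deaths, also, their birth parent", the words *also* and *their* make the birth parent someone other than the research participant. The sentence "Many participants and their birth parents taking part in the trial will have complex medical and mental health histories" likewise names two groups. On this reading the research participant is the child, and the parent is added for deaths only.

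**2. What parents undergo.** They give written consent (Inclusion). A family is excluded if the parent cannot take part in an intervention (Exclusion). NIM assesses every current or prospective carer, and its trial of treatment is directed at the birth family and offered where possible (Intervention description {11a}). Services as usual also assess parenting capacity (Explanation for the choice of comparators {6b}). So procedures that could make a parent's event Related exist in both arms.

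**3. Whether another route to the REC exists.** None was found in the article. The section on the data monitoring committee {21a} has the DMEC report to the funder. Interim analyses {21b} lets the DMEC look at unblinded data and recommend stopping. The section on communicating amendments {25} deals with protocol changes and breach forms.

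**4. Whether the term is used consistently.** It is not. Directly after the sentence that names both groups, the harms section draws a conclusion about events in *the participant group*, which fits best if parents who take part belong to it. Recruitment {15} speaks of a potential participant's competence to consent. Who will be blinded {17a} says participants know their arm. Retention {18b} has participants texting or phoning the team. The children enter at 0 to 60 months, so these sentences describe adults.

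**5. The rule under each reading**, for an SAE judged Related and Unexpected:

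| Event | Participant = child only | Participant includes consenting parents |
|---|---|---|
| Any SAE in the child | to REC | to REC |
| Death of a birth parent | to REC | to REC |
| Non-fatal SAE in a parent who takes part | no stated route | to REC |
| Non-fatal SAE in a parent who does not take part | no stated route | no stated route |

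The third row is the only one on which the readings differ, and it concerns the adults to whom the procedures are applied.

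**6. Logging and DMEC review.** Active capture is by six-monthly review of participants' case notes. The text on logging and six-monthly DMEC review concerns expected events in the participant group. Whether these steps reach non-fatal parental events depends on the same undefined term.

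**The case against.** The strongest reply is that *research participant* already includes parents who consent. Step 4 shows real support for this. The deaths clause would not then be redundant, because it would cover birth parents who did not consent. This stands as a possible reading, so the narrow one is not certain. But the rule's own sentence points the other way, and a safety-reporting rule should not turn on which usage the reader picks.

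A second reply is that the article condenses a full protocol, which may define the term. That limits the point to the article. It does not remove it, because the article states a scope and does not merely leave one out.

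A third is that parents' complex histories make many events expected. The Related-and-Unexpected filter already deals with that, and no reason is given for a further limit to deaths.

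A fourth is that deaths-only reporting is a legitimate choice of scope in a trial with child outcomes, alongside DMEC oversight. It would be easier to accept if parents were not themselves assessed and offered treatment, or if DMEC review of their non-fatal events were clearly stated.

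Stronger readings are tempting but unsupported. A reader might infer that parental events go unrecorded or unreviewed; the text is unclear on this and does not establish it. A reader might infer that NIM harms parents; nothing in the article suggests so. A reader might also size the gap by the number of families in the NIM arm or by the time from the end of recruitment to final follow-up. Neither measures exposure: research and services-as-usual procedures involve parents too, and intervention contact falls mostly early.

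**Conclusion.** The point holds with minor weight. On its most natural reading, the rule denies the REC notice of non-fatal Related and Unexpected SAEs in birth parents who take part. On the wider reading, it is worded ambiguously. The same uncertainty extends to logging and DMEC review.

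The number of affected events cannot be estimated, because the article gives no parental event rate. It is probably small, since an event must be judged both Related and Unexpected to count. The treatment estimate is not affected.

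The conclusion rests on the article alone. It assumes that no definition elsewhere settles who is a research participant for safety reporting.

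**What to change.** Reword the scope of the REC rule along these lines: *an SAE in a research participant or in a birth parent taking part in the trial (and, in the case of deaths, in any birth parent of a participating child)*. This adds non-fatal events in parents who take part and keeps the present cover for deaths of other birth parents.

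Leave the Related-and-Unexpected filter unchanged, so that expected events still stay out of REC reporting. Apply the rule to parental SAEs that come to the study team's attention, and state that these are logged and reviewed by the DMEC in the same way as the children's.

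The cost is one phrase in the protocol and the matching line in the SAE procedure. Consent to parents' health and social work data, the expert panel and the DMEC review are already in place. The downside is a few extra relatedness assessments and an occasional REC report. The benefit falls as intervention contact ends, so the change is worth making promptly.
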